#### Healthy diet B

Healthy diet B will include fruit, vegetables, fish, shellfish, lean meat, nuts, eggs and olive oil. Macronutrient composition and fiber intake will not differ from healthy diet A. GL will also be matched to that of healthy diet A. Healthy diet B will exclude cereal grains, legumes and dairy products, which will largely be replaced by root vegetables (including potatoes), vegetables, fruit and lean meat, and slightly more fish and nuts. Healthy diet B is termed ‘healthy diet without cereal grains and dairy products’. Salt intake will be lower in healthy diet B. This diet is also classified as ‘very healthy’ using validated nutritional software package [32]. It is in accordance with official Spanish dietary recommendations for people with T2DM regarding macronutrient composition, dietary fiber, minerals and vitamins (Tables 1 and 2). A detailed description of each of the meals proposed during the course of one week is included in Additional file 3.

### Dietary design

The main goal of the study is to test the hypothesis that the type of food has an effect on glucose control, independently of macro/micronutrient composition, fiber content, GL and weight loss. Therefore, we generated two different seven-day meal patterns where macro/micronutrient composition and fiber intake are similar. GL is also similar between both seven-day meal patterns. Furthermore, we aim at creating two healthy food patterns, according to official nutritional guidelines in Canary Islands, utilizing a validated nutritional software package (DIAL) [32]. The nutritional composition of the menu plan was analyzed using another validated nutritional software (Dietist XP 3.1; Kost och Näringsdata AB, Bromma, Sweden) to check for possible errors. Minimal differences were observed in the results from both programs. The distribution of macronutrient energy of diets is 19% protein, 28% fat and 53% carbohydrate, and 18% protein, 28% fat, and 53% carbohydrate for healthy diet A and healthy diet B, respectively. The amount of fiber per 2,000 kcal is approximately 48.5 g and 53.1 g in healthy diet A and healthy diet B, respectively. The GL per 2,000 kcal is 116 and 118 in healthy diet A and healthy diet B, respectively. Regarding micronutrient intake, significant differences between the two diets can be seen in Table 2. Importantly, and because one goal of the ADILAN trial is to avoid weight loss, dried fruits were regularly included instead of fresh fruits, in healthy diet B, to match the total weight of food between the two food patterns. Two recent studies have shown that substituting cereal grains for fruits and vegetables increases satiety [19,33], and therefore it may be challenging for the participants to avoid weight loss while adhering to healthy diet B.

### Evaluation

Before and after each intervention period, an oral glucose tolerance test (OGTT) will be performed in the morning after obtaining venous blood samples in the fasting state, and measurements of blood pressure, height (only at the start of intervention 1), weight, waist and hip circumference, sagittal abdominal diameter, triceps, biceps, suprailiac and subscapular skinfolds, at the start and end of both intervention periods will also be taken. The participants will ingest 75 grams of glucose and blood samples will be drawn for glucose and glucagon at 0, 15, 30, 60, 90 and 120 minutes. Areas under the curve (AUC) for plasma glucose (AUC glucose) and glucagon (AUC glucagon) will be calculated. Of great consequence, and for safety reasons, we will assess capillary glucose, using a glucometer, before performing the OGTT. If the result is greater than or equal to 190 mg/dL (10.5 mmol/L) the OGTT will not be performed. Information about participants’ quality of life will be assessed by means of the short form quality of life questionnaire SF-36v2 (standard version), using the validated Spanish version, which will be filled by the participant during each of the OGTT procedures. During the OGTT, at the end of each intervention period, patients will also be asked to give written answers to three open-ended questions about their experience with the dietary pattern that they have been following during the previous four weeks, specifically: ‘What are your thoughts about this diet?’, ‘Describe your positive and negative experiences with this diet’ and ‘How do you think this diet has affected your health?’

During both dietary interventions, free lunch will be provided every day in the kitchen of the Hospital Insular de Lanzarote. Here, our objective is two-fold: a) to control nutrient intake as much as possible and b) to give the participants behavioral support during visits to the hospital.

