### Eligibility

We will include adults (> 18 years old), males and females, with a medical diagnosis of T2DM and increased waist circumference (≥ 80 cm for women and ≥ 94 cm for men), with or without medication (including insulin treatment), with stable weight for three months prior to the start of study, who have received no change in dose of beta blocker or thyroxine for three months prior to the start of study, and no anticoagulant or oral steroid treatment. Inclusion criteria are present glycated hemoglobin (A1c) ≥ 6.0% (≥ 42.1 mmol/mol), with no upper boundary, creatinine < 130 μmol/L and liver enzymes less than four times above the upper reference value.

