#### Secondary outcomes

Fasting plasma glucose, A1c, total cholesterol, LDL cholesterol, HDL cholesterol, triglycerides, high-sensitivity C-reactive protein, blood pressure, and AUCs for glucose and glucagon during OGTT comprise secondary outcomes. Quality of life, assessed with the SF-36v2 questionnaire (standard version), satiety quotient (see below), experience with the dietary patterns and change in medication are also included as secondary outcomes.

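### The OGTT is withheld at high pre-test glucose and the questionnaires are timed to the OGTT, so several secondary outcomes may go missing according to glucose, possibly unequally by diet

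*Protocol article*

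**What the plan says.** All references are to the protocol article.

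- **Evaluation.** An OGTT is planned before and after each four-week period. For safety, "we will assess capillary glucose, using a glucometer, before performing the OGTT", and then: "If the result is greater than or equal to 190 mg/dL (10.5 mmol/L) the OGTT will not be performed".
- **Evaluation, questionnaires.** SF-36v2 is a form "which will be filled by the participant during each of the OGTT procedures". For diet experience: "During the OGTT, at the end of each intervention period, patients will also be asked to give written answers to three open-ended questions". The section names no other occasion for either, and does not say what happens to them when the test is cancelled.
- **Eligibility.** A1c must be at least 6.0%, "with no upper boundary". Insulin-treated patients may enter.
- **Secondary outcomes.** "AUCs for glucose and glucagon during OGTT comprise secondary outcomes". Quality of life is listed as well, and "experience with the dietary patterns and change in medication are also included as secondary outcomes".
- **Primary outcomes.** Fructosamine and glucagon come from fasting venous blood, which is drawn whether or not the glucose load follows.
- **Data analysis.** A paired t-test is planned for effects within subjects and an unpaired t-test for mean outcome values between the diets. The section does not mention withheld tests.

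**The concern.** Whether an AUC exists at a visit is decided by a glucose reading taken minutes earlier. That reading is closely related to AUC glucose and is something the diets are meant to change. The missing values are therefore informative. If one diet lowers glucose, more tests will be withheld on the other diet, and the values lost there will be its highest. A comparison of whatever AUCs remain is then pulled toward no difference.

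The questionnaires raise a separate issue. They do not need the glucose load, yet the written procedure ties them to it. Followed to the letter, a cancelled OGTT also removes that visit's SF-36v2 and, at the end of a period, the diet-experience answers. With 15 participants, and results meant to inform whether larger studies are needed, a few selective losses matter.

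**Working it through.** **1. The plan's own figure.** 190 mg/dL ÷ 18.016 = 10.55 mmol/L, consistent with the stated 10.5. The threshold is not in doubt.

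**2. What depends on the OGTT.**

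| Outcome | Source | Lost if the OGTT is withheld? |
|---|---|---|
| Fructosamine, fasting glucagon (primary) | fasting blood | no |
| Fasting glucose, A1c | blood sample, not the glucose load | no |
| AUC glucose, AUC glucagon | OGTT samples to 120 minutes | yes, necessarily |
| SF-36v2 | form filled in during the OGTT | yes, on a literal reading |
| Diet experience | questions put during the end-of-period OGTT | yes, on a literal reading |

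**3. How many patients remain.** The documents give no rate of readings at or above 190 mg/dL. Let q be an assumed share of visits withheld. Of 15 patients, the number with all four tests is 15(1−q)⁴ if visits are independent and 15(1−q) if the same patients are always affected. The number with both end-of-period visits, under independence, is 15(1−q)².

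| q | all four tests | both end-of-period visits |
|---|---|---|
| 5% | 12.2 to 14.2 | 13.5 |
| 10% | 9.8 to 13.5 | 12.2 |
| 20% | 6.1 to 12.0 | 9.6 |
| 30% | 3.6 to 10.5 | 7.3 |

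**4. Effect on the diet comparison.** All inputs here are assumptions. Fasting glucose stands in for AUC glucose. The diet A mean is μ = 130 to 190 mg/dL, the diet B mean is μ − 15, and the between/within-patient SDs are 45/20 or 30/15. The SD of a single reading is s = √(45² + 20²) = 49.24 or √(30² + 15²) = 33.54.

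For a diet with mean m, let z = (190 − m)/s. The share withheld is 1 − Φ(z), and the mean of the values that remain is m − s·φ(z)/Φ(z).

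Example with μ = 150 and s = 49.24:
- Diet A: z = 40/49.24 = 0.812, withheld 20.8%, remaining mean 132.2.
- Diet B: z = 55/49.24 = 1.117, withheld 13.2%, remaining mean 122.9.
- Unpaired available-case difference: 122.87 − 132.16 = −9.3, against a true −15.

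The complete-pair and change results come from simulating 2,000,000 patients per row. The change column compares end minus start between diets, using every period in which both tests were done.

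| SDs | μ | withheld A / B | unpaired end levels | complete end pairs | change, unpaired | change, all four tests |
|---|---|---|---|---|---|---|
| 45/20 | 130 | 11% / 6% | −11.1 | −14.1 | −14.1 | −14.4 |
| 45/20 | 150 | 21% / 13% | −9.3 | −13.5 | −13.6 | −14.1 |
| 45/20 | 170 | 34% / 24% | −7.5 | −12.9 | −12.9 | −13.7 |
| 45/20 | 190 | 50% / 38% | −6.0 | −12.2 | −12.2 | −13.3 |
| 30/15 | 130 | 4% / 1% | −13.3 | −14.6 | −14.6 | −14.7 |
| 30/15 | 150 | 12% / 5% | −11.2 | −14.0 | −14.0 | −14.3 |
| 30/15 | 170 | 28% / 15% | −8.6 | −13.1 | −13.1 | −13.9 |
| 30/15 | 190 | 50% / 33% | −6.2 | −12.0 | −12.0 | −13.2 |

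Every row shows more tests withheld on the worse diet and an estimate that shrinks toward zero. The shrinkage is large only for the unpaired comparison of levels at high fasting means.

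**The case against.** **The questionnaire loss is inferred.** The text places the forms within the visit; it does not say they are dropped when the glucose drink is withheld. The participant is at the hospital anyway for blood and body measurements. The Data management section has all data registered at baseline and at 4, 10 and 14 weeks without any OGTT condition, and the Design section refers to additional files that are not shown. This stands. A reader might infer that quality of life and experience are collected only during the OGTT and are certain to be lost, but the documents do not say so. What they contain is a procedure tied to a test that may not take place, with no fallback stated.

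**Missing-data handling belongs in the analysis plan.** This stands in part. Silence on withheld AUCs in an article is not in itself a fault. The cancellation rule and the timing of the forms, however, are protocol procedures fixed here, and so is the unpaired comparison of mean values, which is the version most exposed to the rule.

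**The size may be small.** This stands in part. A reader might infer that a true −15 routinely becomes −9 to −6. Those figures need the wider SDs, fasting means of 150 to 190 mg/dL and an unpaired comparison of end-of-period levels. At a mean of 130 the same comparison gives −13.3 to −11.1. The abstract describes several outcomes as changes, and on change most of the effect survives. AUC bias itself was not computed.

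**Only secondary outcomes of a pilot are touched.** True. Glucose control is still measured in the affected patients through fructosamine, fasting glucose and A1c.

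**Conclusion.** The point holds in a limited form. For AUC glucose and AUC glucagon, absence at high pre-test glucose follows directly from the stated rule and can differ between diets. For SF-36v2 and diet experience, the same loss follows only from a literal reading and is a gap to close. That readings at or above the threshold will occur is foreseeable, because entry A1c is uncapped, but their frequency is unknown.

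On the assumed inputs, a true −15 mg/dL appears as about −13 to −6 in an unpaired comparison of available end-of-period levels, and as about −14.7 to −12 within patient or on change. The within-patient figures are only mildly attenuated, but they describe patients below the threshold and not the trial population. These numbers depend on the assumed means, SDs and effect, on fasting glucose as proxy for AUC, and on one capillary reading standing for glucose control on the day. The primary outcomes, fasting glucose and A1c are untouched, and the safety rule is not questioned.

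**What to change.** 1. State in Evaluation that SF-36v2 and the three experience questions are completed at every test visit at which they are due, whether or not the OGTT is performed.
2. Compare AUCs within patient. Report the number of OGTTs withheld under the glucose rule by diet and period, and state that complete-pair AUC glucose and AUC glucagon results apply only to patients below the threshold.
3. As a sensitivity analysis for AUC glucose, rank the two end-of-period tests within each patient, with a test withheld under the glucose rule as the worse result and two withheld tests as tied. Restrict this to end-of-period tests: if ranks were applied to change, a test withheld at the start and performed at the end would count as improvement.

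Leave the safety threshold unchanged. The cost is one procedural sentence and a short addition to Data analysis. The downside is that the rank analysis gives a less direct effect size than a mean difference in AUC, and it does not cover AUC glucagon, for which only the restriction in step 2 applies.

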### Outcome assessment

#### Primary outcomes

The primary outcomes of this study are fasting fructosamine and glucagon. These outcomes will be determined after obtaining venous blood in the fasting state at start and end of each intervention period.

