**Methods/Design:**

We intend to include 15 adult patients with a medical diagnosis of type 2 diabetes mellitus with or without medication and with an increased waist circumference (≥ 80 cm for women and ≥ 94 cm for men) in a random-order cross-over diet intervention study during two periods of four-weeks separated by a six-week washout period. Patients will be instructed to eat two healthy diets according to official dietary guidelines with respect to macro/micronutrient composition and fiber content, but differing in the type of food included, with one diet being without cereal grains and dairy products. Lunch will be served in a hospital kitchen for control of nutrient intake, while the rest of the meals will be eaten at home according to specific directions. The energy content of the diets will be individually adjusted to maintain a stable body weight during the two four-week intervention periods. Primary outcomes will be change in fasting plasma glucagon and fructosamine, while secondary outcomes include change in fasting glucose and glycated hemoglobin, glucose and glucagon response during oral glucose tolerance test, blood lipids, blood pressure, C-reactive protein, body composition, quality of life, subjective experience with the two diets, satiety scores and changes in medication.

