### Power calculations

The predefined primary outcomes are changes in fasting fructosamine and glucagon. In order to detect, with 80% power and at a significance level of 5%, a 26 μmol/L larger reduction in fructosamine after diet B than after diet A, 12 subjects are estimated to be required. For a 37 ng/L difference in change in fasting glucagon between the diets, 13 subjects are estimated to be required.

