### Data management

Study data will be collected and managed using REDCap™ (Research Electronic Data Capture) electronic data capture tools hosted at Lund University [35]. REDCap™ is a secure, web-based application designed to support data capture for research studies, providing: 1) an intuitive interface for validated data entry; 2) audit trails for tracking data manipulation and export procedures; 3) automated export procedures for seamless data downloads to common statistical packages; and 4) procedures for importing data from external sources.

REDCap™ will be configured according to the study protocol in a way that the researchers can register all data at baseline, 4, 10 and 14 weeks after study start. Only the researchers and the hospital nurses will have access to REDCap™. This web application allows for management of the trial without violation of privacy or participant confidentiality and integrity of allocation concealment. The procedure also facilitates supervision from abroad by some of the investigators.

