### Data analysis

Differences in baseline characteristics between the participants will be measured using two-tailed unpaired *t*-tests. A two-tailed paired *t*-test will be used to analyze treatment effects within subjects and a two-tailed unpaired *t*-test will be used to compare mean values of outcome variables between the two diets. Normal Q-Q plots and Shapiro-Wilk test will be performed to check for normal distribution of data. Data transformation will be applied in case the data does not present normal distribution. To test for a possible period effect a two-tailed unpaired *t*-test comparing the mean difference between first and second period for outcome variables and food intake will be performed. To test a possible carry-over effect a two-tailed unpaired *t*-test comparing the average of observations for outcome variables and food intake between the two periods will be performed. *P* < 0.05 will be considered to indicate statistical significance.

Analysis will be conducted by use of SPSS for Mac Version 20 (IBM SPSS Statistics for Mac, Version 20.0. Armonk, NY: IBM Corp.)

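### The primary outcomes are defined and powered as changes, but the analysis section does not say whether changes or end values are compared and plans no adjustment for period-start values, a likely but not certain loss of precision

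*Protocol article*

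**What the plan says.** The abstract of the protocol article (Methods/Design) states "Primary outcomes will be change in fasting plasma glucagon and fructosamine". The Power calculations section agrees: "The predefined primary outcomes are changes in fasting fructosamine and glucagon". It sizes the trial on a between-diet difference in change: 26 μmol/L for fructosamine (12 subjects) and 37 ng/L for glucagon (13 subjects), for 80% power at the 5% level.

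The Primary outcomes section names the two analytes without saying in what form they are analysed. It gives only the sampling times: they are "determined after obtaining venous blood in the fasting state at start and end of each intervention period". The Data management section confirms four time points, since the database will "register all data at baseline, 4, 10 and 14 weeks after study start".

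The Data analysis section names the tests. Effects within a patient get a paired t-test, two-sided. For the comparison of the diets the section says this: "a two-tailed unpaired *t*-test will be used to compare mean values of outcome variables between the two diets". It adds t-tests for period and carry-over effects, and transformation if the data are not normal. It mentions no covariate and does not say whether the outcome variable is a change or an end-of-period value.

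**The concern.** There are two linked problems.

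- **The estimator is not settled.** Two places make change the primary quantity, one gives no form, and the section that names the tests speaks only of mean values. Two analysts following the text could test different quantities for the same primary outcome.
- **Neither version uses the start values well.** In a cross-over each patient is already his or her own control, so the comparison of end values is already free of stable differences between patients. Subtracting a separate start value in each period then brings in the noise of two more measurements. End values alone ignore the start values altogether. Regression on the start-value difference lets the data set the weight.

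The trial plans 15 patients and needs at least 13, so it has little precision to spare. As a pilot for a larger study it should give as tight an estimate as its data allow.

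**Working it through.** **Inputs from the document.** Differences of 26 μmol/L and 37 ng/L, 12 and 13 subjects, 80% power, 5% level, four measurements per patient (weeks 0, 4, 10, 14). No standard deviation (SD) or correlation is given.

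**The plan's own figures.** Without an SD, 12 and 13 cannot be confirmed or refuted; they can only be solved backwards. For a two-sided paired t-test at 80% power (noncentral t), 12 subjects imply an SD of the within-patient difference in change of 27.7 to 29.3 μmol/L. Thirteen subjects imply 41.6 to 43.7 ng/L. The upper glucagon value, 43.7, gives 80% power at 13 patients and is used below.

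**Formulas.** For each patient let X be the start-value difference and Y the end-value difference (diet B minus diet A). Let both have variance V and correlation r.

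- Difference in change, Y − X: variance V + V − 2rV = 2V(1 − r).
- End values only, Y: variance V.
- Y regressed on X: large-sample variance V(1 − r²).
- Adjusted relative to change: V(1 − r²) / [2V(1 − r)] = (1 + r)/2.

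If r1 is the correlation of start and end within a period and r2 the correlation of values across periods, then r = (r1 − r2)/(1 − r2). For example, r1 = 0.8 and r2 = 0.6 give r = 0.2/0.4 = 0.5, and r1 = 0.9 and r2 = 0.7 give r = 0.2/0.3 = 0.67.

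**Small-sample check.** The ratio ignores the cost of estimating the slope and the sequence term. That cost was included by simulating 13 patients (7 and 6 per sequence) with a glucagon difference of 37 and a change-difference SD of 43.7. The adjusted model has 13 − 3 = 10 residual degrees of freedom, against 12 for the paired change test.

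| r (assumed) | Large-sample variance ratio | Power, paired change | Power, adjusted |
|---|---|---|---|
| 0 | 0.50 | 80% | about 95% |
| 0.33 | 0.67 | 80% | about 89% |
| 0.50 | 0.75 | 80% | about 85% |
| 0.67 | 0.83 | 80% | about 82% |
| 0.75 | 0.875 | 80% | about 80% |
| 0.80 | 0.90 | 80% | about 79% |
| 0.90 | 0.95 | 80% | about 77% |

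Type I error of the adjusted model stays near 5%.

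**Where r might lie.** As an illustration only, suppose correlation c(t) decays exponentially with time. The visit schedule then gives r = [2c(4) − c(6) − c(14)] / [2(1 − c(10))]. With a time constant of 5 weeks this is about 0.31. For very slow decay c(t) is close to 1 − t/τ, where τ is the time constant, and r tends to (6 + 14 − 2×4)/(2×10) = 12/20 = 0.60, its upper limit. Larger values need another mechanism, such as strong patient-specific trends, which the document does not exclude.

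**The case against.** The strongest reply is that nothing here is wrong. Order is randomised, so change from period start is an unbiased contrast, and it is also the quantity that was powered. That stands: the issue is efficiency and clarity.

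A second reply is that covariates are often left to a fuller analysis plan. This carries only part of the way, because the article does name its tests and none has a covariate. Nor would a fuller plan remove the difference in wording between the power and analysis sections.

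A third reply is that the gain is not assured. This also stands. A reader might infer that adjustment is free, or that raw change inflates the variance in this trial by 1.2 to 2 times. Those factors are the reciprocals of ratios 0.83 and 0.50, so they hold only for r between 0 and 0.67, and the document gives no correlation. The result that adjustment is never worse is a large-sample one. At 13 patients the gain is gone near r=0.75 and becomes a loss of about 1 to 3 points of power at r=0.8 to 0.9.

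A reader might also infer that the planned analysis has 80% power and that adjustment adds to that. The text does not support this either. The 80% is a paired change benchmark, whereas the test named for comparing diets is unpaired, and it may be meant for end values. The table compares two ways to analyse the cross-over; it does not describe the named test.

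**Conclusion.** The point holds as a cheap precision improvement together with a wording gap. The article makes change the primary quantity in two places, leaves the analysed quantity open in a third, and plans no use of the start values as a covariate. With 13 patients and a paired change analysis at 80% power, adjustment would give about 95% at r=0, 85% at r=0.5 and 82% at r=0.67. It would make no difference near r=0.75 and give about 77% at r=0.9.

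These figures assume normal data, equal variances of the start and end differences, and an SD solved backwards from the stated sample size. The size of the gain, and at high r its sign, depends on a correlation that the document does not give. The possible loss (about 3 points) is small beside the possible gain (about 15 points). The text does not support calling the planned analysis biased or invalid.

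**What to change.** For each primary outcome, take the within-patient difference in end-of-period values (diet B minus diet A) as the response. Regress it on the within-patient difference in period-start values and on sequence coded as a centred term, for example +1/−1, which removes the period effect. Leave the start-value difference uncentred, so that the intercept is the diet effect at equal start values. Report that adjusted difference with its 95% confidence interval.

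State in the Power calculations, Primary outcomes and Data analysis sections that this is the primary analysis, so that all three name the same quantity. Give the SD and correlation assumed behind the figures of 12 and 13.

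The cost is wording, two residual degrees of freedom, and a small loss of power if r exceeds about 0.75. No new data, visits or patients are needed.
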